# Study Protocol

# Title: Randomised controlled feasibility trial evaluating the effectiveness of mindfulness compared to exercise and mindfulness on fatigue in women with gynaecology cancer.

Gynaecology Exercise and Mindfulness Study (GEMS)

Intervention protocol

Section 1 Background and rationale.

Introduction

Gynaecology cancer encompasses ovarian, endometrial, cervical, vaginal, vulva, fallopian tube, and placenta (Lin *et al.* 2016). In the United Kingdom (UK) 21,493 new cases of gynaecological cancer are diagnosed every year (*Gynaecological Cancer Research Charity.* 2020). Treatment modalities can be effective in managing and treating these cancers but may lead to unwanted long term side effects. One side effect is fatigue, the prevalence of which, for all types of cancer, was identified as 52% and for the gynaecology cancer population, this varied between 17-33% with many reporting to experience cancer related fatigue (CRF) many years after treatment (Sekse *et al.* 2015; Ma *et al.* 2020; Sheehan *et al.* 2020a). It has been described not only as a physical sensation but also has emotional and cognitive symptoms suggesting that it is multi-dimensional (McMillan and Newhouse 2011; Coleman *et al.* 2012; de Raaf *et al.* 2013; Dennett *et al.* 2016). To date, few studies evaluate interventions that target all dimensions of fatigue suggesting a multi-modal approach that addresses all aspects is required.

Mechanisms.

Risk factors for CRF that have been described, include depression and insomnia suggesting that the presence of these are not only possibly correlated but may also have an impact on the levels and severity of CRF (Bower 2014). Indeed, the term ‘symptom cluster’ has recently been adopted to describe this and the most common symptoms in this cluster have been identified as depression, insomnia, and fatigue (Payne *et al.* 2008; Oh and Seo 2011; Joly *et al.* 2019). Which suggests that managing fatigue would require the incorporation of interventions that deal with the multiple symptoms of depression, insomnia, and fatigue collectively (Bower 2014; Naraphong *et al.* 2015; Poort *et al.* 2020).

Existing Knowledge

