Mindfulness is the practice of intentional awareness in the present moment without judgement. Its practice encourages participants to develop an awareness of current emotions and thoughts with compassion and kindness and will lead to better control of cognition, emotion, and behaviour (Park *et al.* 2020). Research in cancer demonstrates the positive effects of mindfulness on both CRF and QOL and recommend it as an intervention (Leydon *et al.* 2012; Van Der Lee, and Garssen 2012; Lengacher *et al.* 2012; Bruggeman-Everts *et al.* 2015; Johns, S. A. *et al.* 2015; Huang, H. -. *et al.* 2016; Johns, S. A. *et al.* 2016; Lengacher *et al.* 2017; Reich *et al.* 2017a; Zhang, Qiuxiang *et al.* 2019; Xie *et al.* 2020; Xunlin *et al.* 2020; Park *et al.* 2020). Though some of the effect sizes shown in studies were small and did not reach minimal clinical significance, there was still however an effect on psychological distress, which is defined as an emotion that is not pleasant (Cramer *et al.* 2012; Haller *et al.* 2017; Cillessen *et al.* 2019). This effect on the psychological distress and particularly on the symptoms of anxiety, depression, sleep, stress, and quality of life have been shown to significantly improve following the introduction of mindfulness (Carlson and Garland 2005; Huang, J. and Shi 2016; Reich *et al.* 2017b). Some of these symptoms are also present within the ‘cluster symptoms’ previously identified suggesting that there may also be an improvement in fatigue alongside these symptoms.

Need for a trial

Most of the current studies that involve exercise or mindfulness for the management of CRF and psychological distress tend to be in the breast cancer population making it difficult to generalise findings to other cancer populations (Brandenbarg *et al.* 2018; Stelten *et al.* 2020). It would appear that both exercise and mindfulness have individually as interventions demonstrated positive effects on CRF, anxiety, depression, and sleep. Whether mindfulness and indeed adding mindfulness to an exercise regime for managing fatigue in women with gynaecology cancer is of benefit, is yet to be explored. Therefore, this study will aim to assess how feasible and acceptable the interventions, mindfulness, and exercise, will be and if there is any effect on fatigue for the gynaecology cancer patient.

Primary Aim

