To explore the feasibility of conducting an 8- week online mindfulness and home-based walking and strength training programme for the management of cancer related fatigue in women with gynaecology cancer. The following objectives will assess feasibility outcomes:

1. To assess participant intervention adherence, study retention and attrition rate.
2. Explore the acceptability of using an online platform for the delivery and data collection of the exercise and mindfulness programme.
3. Explore the perspectives of participants concerning satisfaction (eg the intervention and its’ delivery) perceived value, barriers and facilitators of the online programme.

Secondary aim

To evaluate the effect of an 8 week exercise and mindfulness programme on cancer related fatigue as a primary clinical outcome and the effect on anxiety, depression, sleep and QoL as a secondary clinical outcome in an online setting.

Section 2 Methods

Study design

The study design and development have been reviewed and feedback considered from 2 patient and public involvement representatives.

This design will involve 2 parts firstly, an intervention part which is designed as an open, randomised, control trial with 1:1 allocation to either the mindfulness only group or the exercise and mindfulness group.

Following the intervention the second part will be online focus groups which will be conducted with participants once they have completed the intervention.

Study setting

Both parts of this study, intervention and focus groups, will be conducted online via a web-based, mobile application interface. Participants will be notified that data usage with this app will be minimal and battery usage of mobile devices may increase requiring additional charging of device. Therefore, participants should not incur any additional financial burden.

Participants & Eligibility

Eligibility criteria:

Inclusion criteria:

1. Women >18 years old and able to speak and read English.
2. Diagnosed with stage I-IV gynaecology cancer including endometrial, ovarian, cervical, vaginal, vulva, fallopian tube.
3. A minimum of 3 months post-treatment and up to 5 years.
4. Experiencing fatigue and at screening have a numerical rating score of $\geq$4 on a scale of 0-10.
5. Currently sedentary (exercising < once a week for 20 minutes at a vigorous intensity or, two times per week for 30 minutes at moderate intensity or < 20 minutes three times per week, for the past 6 months).

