**Statistical methods**

Descriptive statistics will be performed to produce mean values and standard deviations. Groups will be compared at baseline using independent t-test (two independent samples) for continuous data, and the chi-square test for independence for categorical data.

Primary analyses will be performed using the intention to treat on all data and using imputation method where outcomes are missing. Alpha will be set a priori at a level of P = .05. Repeated-measures ANOVAs will then be used to determine the effects of exercise and mindfulness and mindfulness intervention on changes in all outcomes of interest.

As this is a feasibility study and preliminary efficacy study, effect sizes (Cohen’s d) will be calculated by taking the mean difference and dividing by the pooled standard deviation to better estimate the meaningfulness of change for each observed outcome following the intervention. The values and meanings for effect size estimates are a small effect size (d = .2), a moderate effect size (d = .5), and a large effect size (d = .8).

Corelation analysis will be performed to determine whether changes in mindfulness/exercise are associated with changes in fatigue, anxiety, depression or sleep.

References.

Craig, P.e.a. (2019) Medical Research Council Developing and
evaluating complex
interventions.

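### Both arms receive mindfulness, so the secondary aim and the analysis sentence should be narrowed to the effect of adding exercise to mindfulness

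*Protocol*

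**What the plan says.** Five places in the Protocol bear on which effect the trial is meant to estimate.

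- **Title:** it promises a study "evaluating the effectiveness of mindfulness compared to exercise and mindfulness on fatigue". This names the two arms as they are.
- **Need for a trial:** two gaps are given. One is the value of mindfulness itself. The other is put as follows: "adding mindfulness to an exercise regime for managing fatigue in women with gynaecology cancer is of benefit, is yet to be explored". The section goes on to draw its feasibility and fatigue questions from these gaps.
- **Primary aim:** this concerns feasibility and needs no contrast between the arms. It begins "To explore the feasibility of conducting an 8- week online mindfulness and home-based walking and strength training programme".
- **Secondary aim:** no comparator is named here. The sentence opens "To evaluate the effect of an 8 week exercise and mindfulness programme on cancer related fatigue as a primary clinical outcome". The other four patient-reported measures that it lists rank below fatigue.
- **Study design:** randomisation is by "1:1 allocation to either the mindfulness only group or the exercise and mindfulness group". Nobody is assigned to exercise alone, and nobody is left without either component.

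Statistical methods then gives the purpose of its ANOVAs, which is "to determine the effects of exercise and mindfulness and mindfulness intervention on changes in all outcomes of interest". Alpha is .05, and Cohen's d is planned for each outcome.

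**The concern.** The rationale asks what mindfulness does, alone or on top of exercise. The secondary aim asks what the combined programme does. The analysis sentence says the effects of both interventions will be determined. The randomisation answers none of these. It answers what exercise adds when everyone already has mindfulness, which is the reverse of the second question in the rationale.

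The stake is in how the results are read. If the stated aim is followed literally, the only route to an effect of the programme, or of mindfulness, is before-after change within an arm. That change is uncontrolled. Entry requires a fatigue score of at least 4 out of 10 (inclusion criterion 4), so some improvement through regression to the mean is possible with no treatment effect at all. A null between-arm difference is also open to misreading, because it is compatible with a programme that helps both arms equally through mindfulness.

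**Working it through.** **Inputs.** The arms are from Study design. The sample size (20 per arm, 40 in total) is from Sample size, and attrition of about 20% is from the Primary Outcome list. The benchmarks of 0.2, 0.5 and 0.8 and alpha of .05 are from Statistical methods. The Protocol bases its 40 on the size of similar feasibility studies, so it has no power figure to reproduce; 20 + 20 = 40 agrees.

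**Which effects are identified.** Let b be background change (natural course plus regression to the mean), m the effect of mindfulness alone, x the effect of exercise alone and i their interaction.

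- Mean change, mindfulness only: b + m
- Mean change, exercise and mindfulness: b + m + x + i
- Difference: (b + m + x + i) − (b + m) = x + i. Call this e, the effect of exercise given on top of mindfulness.

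| Question | Quantity | Identified? |
|---|---|---|
| Is mindfulness of benefit? (Need for a trial) | m | No |
| Is mindfulness added to exercise of benefit? (Need for a trial) | m + i | No; needs an exercise-only arm |
| What is the effect of the combined programme? (Secondary aim, if read against no programme) | m + x + i | No; needs an arm without either component |
| Mindfulness compared with exercise and mindfulness (Title) | x + i = e | Yes |

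Two arm means cannot separate four unknowns. Only their difference is free of b.

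**Does before-after change help?** The two-arm, two-time-point design was simulated with 20 per arm and 20,000 runs per case. Assumptions: SD 1, pre-post correlation 0.5 and a two-sided test at 0.05. The SD of change is then √(2 × (1 − 0.5)) = 1.

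| Assumed truth | Between-arm difference | Group-by-time significant | Time effect significant | Within-arm change significant, combined arm |
|---|---|---|---|---|
| b = 0, m = 0.5, e = 0 | 0.00 | 5% | 87% | 57% |
| b = 0.5, m = 0, e = 0 | 0.00 | 5% | 87% | 57% |
| b = 0, m = 0.5, e = 0.3 | 0.30 | 15% | 98% | 92% |

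In the first row mindfulness works; in the second nothing works. The results are the same. In the third row the combined arm improves by 0.80, of which the randomised contrast recovers 0.30.

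**Precision of the contrast that is identified.** The 95% half-width for a standardised difference is t × √(2/n). At n = 20 this is 2.024 × √(2/20) = 0.64. At n = 20 × 0.8 = 16 it is 2.042 × √(2/16) = 0.72. Power at d = 0.2, 0.5 and 0.8 with 20 per arm is 10%, 34% and 69% (noncentral t). Rewording the aim changes none of these figures.

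**The case against.** The best defence is that the Protocol already states the true contrast. The title compares mindfulness with exercise and mindfulness, Study design gives the same two arms, and the secondary aim can be read in that light as relative to mindfulness only. The phrase in the rationale is background rather than an objective, and the ANOVA sentence may simply be listing the two arms. The trial calls itself a feasibility and preliminary efficacy study, with no efficacy hypothesis or success rule.

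Much of this stands. The title is right, and the missing comparator makes the secondary aim ambiguous rather than plainly a claim against no treatment. But the aim does not state the comparator, and the analysis sentence, taken at its word, includes an effect of the mindfulness intervention itself. The planned correlation of changes in mindfulness or exercise with changes in symptoms is not randomised, so it does not supply that effect.

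Three stronger readings are tempting and not supported:

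- **That the trial as a whole is misdirected.** The primary aim is feasibility, and adherence, attrition, recruitment and acceptability do not depend on the between-arm contrast.
- **That a positive difference would show mindfulness contributes nothing.** With m = 0, x = 0 and i = 0.5 the contrast is 0.5, and adding mindfulness to exercise is also worth 0.5. With m = 0, x = 0.5 and i = 0 the contrast is again 0.5, and adding mindfulness is worth 0. The trial cannot tell these apart. The Protocol's own background suggests mindfulness may ease psychological barriers to exercise such as motivation, so an interaction is plausible.
- **That the results will be misreported.** The documents do not show this. The wording leaves it open.

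**Conclusion.** The point holds for the secondary efficacy aim, the analysis sentence and one phrase in the rationale. The randomised comparison estimates the effect of adding exercise to mindfulness, interaction included, and nothing else. That follows from the arms alone and does not depend on the assumed SD, correlation or effect values, which serve only for illustration. There is no trial-specific size of error, because the Protocol gives no expected effects: the gap between the whole-programme effect and the randomised contrast equals m, whatever m is. The change is worth making, because it settles what the trial may conclude about fatigue, its primary clinical outcome. It is a mismatch between stated aim and design that wording can cure, and it does not call for a new arm.

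**What to change.** 1. **Secondary aim.** Reword to: *to estimate the effect of adding the 8-week home-based walking and strength programme to online mindfulness, compared with mindfulness only, on cancer-related fatigue (primary clinical outcome) and on anxiety, depression, sleep and quality of life (secondary clinical outcomes).* Keeping every outcome in the sentence avoids dropping any by accident.
2. **Statistical methods.** State that, for every outcome of interest, the effect is the group-by-time term, that is, the between-arm difference in change. Add that within-arm changes and within-arm effect sizes are descriptive and do not estimate the effect of mindfulness or of the programme.
3. **Need for a trial.** Change the phrase to *adding exercise to mindfulness*.

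These are Protocol wording changes only. Arms, randomisation, sample size, outcomes and the feasibility aim stay as they are. The one cost is a narrower efficacy claim.

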If participants are interested in the study they can self-refer and a contact number for the researcher will be made available through the leaflets, social media or service providers. Participants can call the researcher for further information and if willing and interested screening for eligibility will be performed by the researcher (appendix 3). Once this is complete and it is established that participants meet the criteria participants will be e-mailed participant information sheet by the researcher (appendix 4) and time given to read and ask any questions regarding this. Participants can contact the research team if they have any further questions. Consent (Appendix 5) will be obtained after participants have been given one week to consider the study. An Qualtrics link to an electronic version of the consent will be emailed to participants.

Randomisation

Participants will be randomly allocated to either group through 1:1 allocation. Participants will be randomly assigned using computer-generated random number tables. A researcher/statistician not involved in treatment delivery or collection of outcomes will generate the random allocation sequence. Concealment of treatment allocation will be by placing individual random assignments into serially numbered sealed envelopes and be held by researcher/statistician not involved in treatment or outcome measure collection.

Participants will be notified of which group they have been allocated to via the e-mail they have supplied. A member of the research team will e-mail the participant with this information.

Data collection methods

Outcome measures

Data collection for outcome measures will be self-report measures using valid and reliable tools for measuring these outcomes. Participants will be asked to complete these assessments following randomisation at baseline and on completion of the programme. At baseline participants will also complete demographic information such as age, cancer type, education, income, and education (appendix 6). All of this will be done via Qualtrics (appendix 7), an e-mail reminder will be sent 2 weeks after the initial invitation if completion has not occurred. Access to intervention will only happen once all baseline assessments have been completed.

The following self-report measures will be used to assess outcomes at baseline and post-intervention (copies and links to Qualtrics of all can be found in appendix 7).

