**Sample size**

The sample size for this study is based upon feasibility and review of similar studies. The literature demonstrates that feasibility studies with similar interventions and methodologies within the cancer population recruit on average 40 participants in total (Eyles *et al.* 2015; Victorson *et al.* 2017; Price-Blackshear *et al.* 2020). Therefore it is anticipated that this study will recruit a total of 40 participants with 20 in each arm of the study.

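### Baseline questionnaires follow randomisation in an open, self-report trial, with no rule that the allocation e-mail waits for them

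*Protocol*

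**What the plan says.** Section 2, Study design, describes "an intervention part which is designed as an open, randomised, control trial". Under Randomisation, "Participants will be notified of which group they have been allocated to via the e-mail they have supplied"; the timing of that e-mail relative to the questionnaires is not given.

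Under Data collection methods, Outcome measures: "Data collection for outcome measures will be self-report measures using valid and reliable tools for measuring these outcomes". The order is then fixed: "Participants will be asked to complete these assessments following randomisation at baseline and on completion of the programme". Completion is remote, through Qualtrics, and "an e-mail reminder will be sent 2 weeks after the initial invitation if completion has not occurred"; no closing date is set. There is one gate: "Access to intervention will only happen once all baseline assessments have been completed".

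Appendix 14 places eligibility screening and consent under Enrolment. FACIT-F, FACT-G, PSQI, FFMQ, HADS and IPAQ-SF are marked under Allocation (time 0) and again at close-out. Demographics alone is marked under both Enrolment and Allocation.

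Statistical methods plans an intention-to-treat analysis with imputation of missing outcomes, and repeated-measures ANOVAs on change in all outcomes. Primary Outcome lists adherence, attrition and retention among the feasibility outcomes. It expects about 20% attrition and says that these outcomes concern women who completed or took part in the intervention.

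**The concern.** A woman who knows whether she has been given exercise as well as mindfulness may answer questions on fatigue, mood or activity differently from one who does not know. If that happens at baseline, the measurement that anchors every change analysis is no longer independent of the arm. A baseline difference created by disclosure can then appear as a difference in change between arms.

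The second consequence does not depend on reporting behaviour. A woman who is randomised but never completes baseline is not given access to the intervention and has no baseline value, yet she belongs to the intention-to-treat set. Retention and attrition are primary feasibility outcomes, so it matters whether she is in their denominator.

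Neither problem can be repaired after data collection. The order is stated in the protocol itself, so this is not a detail left to a later analysis plan.

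**Working it through.** **Order of events.** The protocol text and Appendix 14 agree: screening, consent, randomisation, baseline scales, access to the app. Baseline therefore precedes exposure to the intervention. No sentence makes it precede knowledge of the allocation. The only timing device is a reminder at 2 weeks, so the interval between allocation and baseline can be two weeks or more.

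**Plan's own figures.** The Sample size section states that "it is anticipated that this study will recruit a total of 40 participants with 20 in each arm of the study". This rests on the size of similar studies; there is no power calculation to reproduce. 20 + 20 = 40 is consistent, and 20% attrition is 0.20 × 40 = 8 women, leaving 32, or 16 per arm.

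**Effect of a baseline shift (assumed).** With two time points, the group-by-time term is the difference in mean change:

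Δ = (post₁ − base₁) − (post₂ − base₂).

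If disclosure moves base₁ by b and leaves all follow-up values alone, Δ moves by −b. With b = 0.2 SD the bias is 0.2 SD in size, which equals the value that Statistical methods labels a small effect. If the same shift persists at follow-up, Δ moves by b − b = 0.

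To see what this does to a test at 0.05 (two-sided assumed), take no true effect and a baseline-to-follow-up correlation ρ of 0.5 to 0.7 (assumed). The SD of change is √(2(1−ρ)), in units of the outcome SD. The noncentrality is b / [√(2(1−ρ)) × √(2/n)].

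- n = 20 per arm, b = 0.2: 0.2/(1.000 × 0.316) = 0.63 at ρ = 0.5, and 0.2/(0.775 × 0.316) = 0.82 at ρ = 0.7.
- The noncentral t distribution then gives these rejection rates:

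| Assumed b (SD) | 20 per arm | 16 per arm |
|---|---|---|
| 0 | 0.050 | 0.050 |
| 0.1 | 0.061–0.068 | 0.059–0.064 |
| 0.2 | 0.095–0.125 | 0.085–0.109 |
| 0.3 | 0.152–0.223 | 0.130–0.185 |

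Baseline-adjusted ANCOVA would reduce the bias to ρ × b, that is 0.5 × 0.2 = 0.10 to 0.7 × 0.2 = 0.14 SD, but would not remove it.

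**Effect of loss before baseline (assumed).** If 5–15% of randomised women never complete baseline, that is 0.05 × 40 = 2 to 0.15 × 40 = 6 women, against the 8 expected from all attrition. As an illustration in one arm, suppose 2 of 20 never complete baseline and 4 leave later. Retention is 14/20 = 70% of those randomised, or 14/18 = 78% of those with a baseline.

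**The case against.** The case on the other side is substantial.

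- **A reader might infer that women learn their arm before completing baseline.** The documents do not say so. Randomisation is described before data collection, but the order of description is not a timetable. What stands is that nothing prevents it.
- **A reader might infer that every baseline item falls after allocation.** Demographics is also marked at Enrolment. What stands concerns the six outcome scales.
- **A reader might infer that early losses are counted as intervention attrition.** Primary Outcome does not say this. Its restriction to women who took part could exclude them. It also gathers recruitment and retention data at each stage, including allocation and follow-up, so such losses could be identified. What stands is that the denominator is unclear. Nor does the protocol say that a woman without a baseline would be refused the post-programme questionnaires.
- **The 0.2 SD has no source in the documents.** It passes in full only if follow-up reporting is unaffected, and follow-up is also open self-report. Both arms receive mindfulness, and most scales ask about the past week (PSQI about the past month), so a shift may be small. With 20 per arm and ρ of 0.5–0.7, the standard error of Δ is 1.000 × 0.316 = 0.32 to 0.775 × 0.316 = 0.25 SD, so 0.2 SD is below one standard error.
- **The access gate is a real protection.** It keeps baseline free of app content. It does not cover knowledge of allocation or loss before baseline.
- **Efficacy is a secondary aim in a feasibility study.** This lowers the severity. It does not touch the primary retention and attrition outcomes.

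**Conclusion.** The point holds as a design weakness of moderate severity. The protocol places all self-report outcome scales after randomisation in an open trial and leaves open the possibility that allocation is already known when they are completed. Women can also be lost between allocation and baseline, without a baseline value but within the intention-to-treat set.

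The size and direction of any reporting shift cannot be told from the documents. The 0.2 SD bias is an illustration that assumes a shift at baseline only, in one arm. The 2–6 women rest on an assumed 5–15% loss. The finding itself needs neither figure: it rests on the stated order, the missing rule on disclosure and the unclear denominator.

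It would go too far to conclude that baseline will be biased or that the trial cannot proceed as written. The case for acting is that the change is nearly free now and unavailable once data have been collected.

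**What to change.** 1. In Data collection methods, state that all baseline questionnaires are completed in Qualtrics after consent and before the next envelope is opened, and that only women with a completed baseline are randomised.
2. In Appendix 14, move the baseline marks for the six outcome scales from Allocation to Enrolment.
3. Under Randomisation, state that the allocation e-mail and the app link are sent only after that. Align the description of the mindfulness intervention, which sends the portal link to screened, consented and randomised women without repeating the baseline condition.
4. In Primary Outcome, define retention and attrition with all randomised women as the denominator, and report consented-but-not-randomised women separately.

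The cost is protocol wording and one column of a table. The sample size, instruments, staff, Qualtrics system and envelopes are unchanged. The downside is that some early loss moves ahead of randomisation and so leaves the retention figure, which is why item 4 is needed.

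A smaller change, withholding the allocation e-mail until baseline is complete, would deal with knowledge of allocation but not with loss between allocation and baseline. If that route is taken, those losses should be reported by arm.
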